## Abstract

**Introduction:**

Postpartum low back pain (PLBP) is common among puerperal women, with complex etiology involving spinal-pelvic changes and reduced core stability. It often becomes chronic, impairing quality of life and mental health. Non-pharmacological therapies are widely used and show good outcomes, but high-quality RCTs are limited, and objective evidence of core muscle activation after combined manual therapy and Baduanjin is lacking. Baduanjin is a traditional Chinese mind-body exercise that uses gentle movements and coordinated breathing to enhance core stability, making it particularly suitable for postpartum women. Previous studies have demonstrated its effectiveness in reducing pain and improving function in patients with chronic low back pain, with preliminary evidence also supporting its benefits in the postpartum population. This gap undermines the protocol's credibility and clinical uptake. Therefore, this study aims to evaluate the efficacy of lumbopelvic manipulation plus Baduanjin for PLBP, and to explore neuromuscular mechanisms using surface electromyography (sEMG).

**Methods and analysis:**

This single-center, assessor-blinded RCT will enroll 50 participants randomized 1:1 to control (health education + lumbopelvic manipulation) or experimental group (same plus Baduanjin). The control group will receive lumbopelvic manipulation (15 min/session, three times per week), while the experimental group will receive the same manipulation plus supervised Baduanjin exercise (12 min/session, three times per week) for 4 weeks. The 4-week intervention is followed by follow-up assessments at weeks 8 and 12. Primary outcome: pain intensity (Numerical Pain Rating Scale, NPRS). Secondary outcomes: functional disability (Oswestry Disability Index, ODI), quality of life (SF-36), and sEMG parameters (%MVIC and mean power frequency, MPF) of the lumbar extensors (erector spinae and multifidus) and abdominal wall muscles (rectus abdominis, external/internal oblique, and transversus abdominis). Assessments at baseline (week 0) and week 4; NPRS, ODI, SF-36 also at weeks 8 and 12.

**Discussion:**

This trial will evaluate the efficacy of lumbopelvic manipulation combined with Baduanjin exercise for postpartum low back pain, a population with limited medication options during lactation. The inclusion of sEMG alongside patient-reported outcomes will provide objective evidence on neuromuscular changes, extending current evidence that has relied primarily on subjective measures.

**Clinical Trial Registration:**
https://itmctr.ccebtcm.org.cn, identifier: ITMCTR2025001056.

## Introduction

1

Postpartum low back pain (PLBP) is defined as recurrent or continuous pain localized to the lumbar and lumbosacral spine, with or without referral to the gluteal region, that occurs after childbirth (1). This condition significantly impairs a mother's ability to perform daily activities and care for her infant, serving as a major contributor to postpartum disability (2). Miladi et al. (1) reported that approximately 53% of women suffer from this pain during the early postpartum period, whereas Alqabbani et al. (2) demonstrated that the prevalence can reach up to 71% within the first year after delivery. Moreover, Bergström et al. (3) found that a considerable proportion of women still experience persistent or recurrent pain up to 14 months postpartum. Although previous studies have identified risk factors such as a history of low back pain, effective evidence-based non-pharmacological interventions for PLBP remain scarce (1), and the underlying mechanisms are not yet fully understood.

Interventions for spinal and pelvic-derived low back pain are generally classified into three categories: pharmacological, non-pharmacological, and invasive procedures (4). Despite this classification, PLBP as a distinct subgroup remains inadequately managed (5). As most patients are breastfeeding, medications may cause adverse effects in infants via breast milk, and many drugs are contraindicated during lactation (6). Therefore, non-pharmacological therapies are considered the first-line treatment for PLBP (7). Although PLBP shares some clinical features with pelvic girdle pain (PGP), the two conditions are distinct in terms of pain location, aggravating factors, and underlying biomechanical mechanisms. Focusing on PLBP as a specific clinical entity allows for a more homogeneous study population and clearer interpretation of the intervention effects on lumbar core muscle function.

Manual therapy can rapidly correct joint malalignment, relieve pain, and improve range of motion, making it a common clinical approach. Nevertheless, manual therapy alone often provides only short-term relief and has limited effects on improving active stability in patients with chronic non-specific low back pain (8). Similar findings have been reported in postpartum populations, although the evidence remains limited (9). In contrast, exercise therapy focuses on neuromuscular control and core stability reconstruction (10). Through active muscle contraction training, it enhances the strength of lumbopelvic stabilizers (e.g., multifidus and erector spinae), thereby improving the dynamic stability of the lumbopelvic region (11). Various forms of exercise therapy—including walking, yoga, Pilates, strengthening exercises, and core stabilization training—have been investigated for managing low back pain, with systematic reviews supporting their beneficial effects on pain reduction and functional improvement (9). However, many of these approaches may be challenging for postpartum women due to the need for specialized equipment, high physical demands, or restrictions during the early recovery period (12). In contrast, Baduanjin is a traditional Chinese mind-body exercise that requires no equipment and consists of gentle, low-impact movements coordinated with breathing. Its focus on core stability and neuromuscular control, combined with its ease of learning and home-based practice, makes it particularly accessible for postpartum women. In our previous study, Baduanjin significantly reduced pain and improved proprioception in patients with postpartum low back pain (13), supporting its potential in this population.

Despite these findings, existing studies on PLBP interventions have notable limitations. Most investigations report only subjective outcomes (e.g., pain scores and functional questionnaires) and lack objective assessments of muscle activation levels (14). Moreover, although both manual therapy and exercise have demonstrated benefits independently, emerging evidence suggests that combining these approaches may yield additional therapeutic gains. Our previous study, for example, found that Baduanjin combined with routine lumbopelvic manipulation significantly improved pain and proprioceptive function compared with manipulation alone in patients with postpartum low back pain (13). Conceptually, manual therapy is thought to correct joint malalignment and alleviate pain, thereby creating a more favorable biomechanical environment, whereas Baduanjin exercise targets neuromuscular control and core stability. Their combination may thus offer complementary benefits through a “prepare-then-train” sequence (15). However, the specific synergistic mechanisms of combined manual therapy and Baduanjin exercise remain incompletely understood, and studies systematically evaluating such combinations are still limited (16).

Given this background, the present study integrates lumbopelvic manipulation with Baduanjin exercise. In addition to subjective measures (Numerical Pain Rating Scale, NPRS; Oswestry Disability Index, ODI), surface electromyography (sEMG) will be used to objectively quantify changes in muscle activation and fatigue resistance of the lumbopelvic stabilizers—including the erector spinae, multifidus, rectus abdominis, external oblique, internal oblique, and transversus abdominis—using parameters including %MVIC (normalized root mean square expressed as a percentage of maximum voluntary isometric contraction) and mean power frequency (MPF). A comprehensive literature search of PubMed, Web of Science, and CNKI databases using the keywords “lumbopelvic manipulation,” “Baduanjin,” “postpartum low back pain,” and “surface electromyography” revealed no previous studies specifically investigating this combination. To the best of our knowledge, limited evidence exists regarding the combination of lumbopelvic manipulation with Baduanjin exercise for PLBP using sEMG as an objective outcome measure. Specifically, it remains unclear whether combining lumbopelvic manipulation with Baduanjin exercise can improve core muscle activation and neuromuscular function in postpartum women, as most existing studies have relied on subjective outcomes and have not systematically evaluated this combined approach.

## Methods

2

### Trial design

2.1

This is a single-center, assessor-blinded, randomized controlled trial in which 50 eligible participants will be randomly assigned in a 1:1 ratio to receive either the control or the experimental intervention. The study will last 12 weeks in total, consisting of a 4-week therapeutic intervention phase (weeks 0–4) followed by an 8-week follow-up period (weeks 4–12).

This trial was registered with the International Traditional Medicine Clinical Trial Registry (ITMCTR2025001056) on 22 April 2025. The protocol conforms to the SPIRIT 2013 reporting guidelines, with the completed checklist provided in the Supplementary material. Figure 1 presents the trial flow diagram, and Table 1 outlines the comprehensive study schedule.

**Figure 1 F1:**
[figure not shown]
Trial flow diagram.

**Table 1 T1:** Trial schedule.

Study period	Enrolment	Intervention	Follow-up	
Time point	Baseline (Week 0)	Week 4	Week 8	Week 12
Eligibility screen	√			
Informed consent	√			
Randomization/allocation	√			
Intervention manipulation		1–4 weeks		
NPRS	√	√	√	√
ODI	√	√	√	√
SF-36	√	√	√	√
sEMG	√	√		
Adverse events monitoring	Any time during the intervention and follow-up			

√, required; NPRS, Numerical Rating Scale; ODI, Oswestry Disability Index; SF-36, 36-Item Short Form Health Survey; sEMG, Surface electromyography.

The primary objective of this study is to evaluate the efficacy of lumbopelvic manipulation combined with Baduanjin exercise for reducing pain and improving functional outcomes in patients with postpartum low back pain. The secondary objective is to explore the neuromuscular mechanisms underlying this combined intervention using surface electromyography.

### Ethics approval and consent to participate

2.2

This study was approved by the Ethics Committee of the Rehabilitation Hospital Affiliated to Fujian University of Traditional Chinese Medicine (approval No. 2025KY-005-01, dated 31 March 2025). The research will be conducted in accordance with the Declaration of Helsinki (2013 revision) and the relevant regulations of the National Health Commission of the People's Republic of China. All eligible participants will receive a full explanation of the study's purpose, procedures, potential risks and benefits, and their right to withdraw at any time without penalty. Written informed consent will be obtained from each participant prior to any study-specific procedures. The informed consent form will be signed and dated by both the participant and the investigator, with one copy retained by the participant. All participant data will be anonymized and stored in a password-protected electronic database accessible only to the research team. These procedures comply with the relevant data protection regulations of the People's Republic of China, including the Personal Information Protection Law.

### Recruitment

2.3

This study will be conducted at the Department of Pelvic Floor Rehabilitation and the Department of Tuina of the Rehabilitation Hospital Affiliated to Fujian University of Traditional Chinese Medicine. A multimodal recruitment strategy, incorporating social media platforms (WeChat) and posters displayed in hospitals and community service centers, will be employed to ensure sufficient participant enrollment. Recruitment is expected to take approximately 4–6 months, with the goal of enrolling 50 eligible participants.

### Eligibility criteria

2.4

#### Diagnostic criteria for postpartum low back pain

2.4.1

Given the absence of standardized diagnostic criteria specifically for PLBP, we adapted the diagnostic framework from contemporary clinical practice guidelines for the management of low back pain (17). All of the following conditions must be met to ensure the specificity of the diagnosis within the postpartum population:

(1) Onset of low back pain within one year after delivery (18);(2) Pain localized below the 12th rib and involving the lumbar and lumbosacral spine, with or without referral to the gluteal region;(3) Pain predominantly dull or aching in nature;(4) Aggravation by prolonged sitting or standing, heavy lifting, or bending, and relief by rest or treatment;(5) Imaging examinations (e.g., X-ray or MRI) may be performed when clinically indicated to rule out serious underlying pathologies (e.g., fracture, infection, or malignancy).

Participants with predominant features of pelvic girdle pain—such as pain localized to the sacroiliac joints or pubic symphysis, aggravated by weight-bearing activities—will be excluded to ensure a homogeneous PLBP population.

#### Inclusion criteria

2.4.2

(1) Participants will be aged 20 to 40 years (inclusive) (19); (2) Participants will have an NPRS score of ≥ 3 at baseline, indicating at least mild to moderate pain intensity, to ensure sufficient room for improvement and clinical relevance. (3) Participants will be primiparous or secundiparous women who have experienced low back pain within 1 year after delivery; (4) Participants will voluntarily enroll in the study and sign the informed consent form; (5) Participants will not use any unrelated physiotherapy or related medications during the treatment period.

The age range of 20–40 years was chosen to focus on the typical reproductive age window and to minimize confounding from age-related physiological differences that could influence treatment outcomes. Similarly, the inclusion was restricted to primiparous and secundiparous women to reduce heterogeneity arising from cumulative biomechanical and neuromuscular changes associated with higher parity, which may affect lumbopelvic stability and treatment responses. While we acknowledge that these criteria may limit generalizability, they were implemented to enhance the internal validity of this proof-of-concept study.

#### Exclusion criteria

2.4.3

(1) Lumbar tuberculosis, lumbar spinal stenosis, or a history of lumbar spine surgery;(2) Presence of severe systemic comorbidities, including uncontrolled hypertension, diabetes mellitus with end-organ complications, severe cardiovascular or cerebrovascular disease, or other conditions that, in the investigator's judgment, would contraindicate participation or interfere with the study procedures;(3) Special populations, including individuals with major psychiatric disorders (e.g., schizophrenia, bipolar disorder, or severe major depression) that, in the investigator's judgment, would impair their ability to provide informed consent, comply with the study protocol, or complete the outcome assessments; deafness, or mutism;(4) Current participation in other clinical trials.

#### Withdrawal/dropout criteria

2.4.4

(1) Participants are found not to meet the inclusion criteria after enrollment; (2) Adherence to the intervention protocol falls below 80% (i.e., missing more than 2 of the 12 scheduled manipulation sessions, or more than 5 of the 28 scheduled Baduanjin sessions), without a valid reason documented by the investigator. Missed sessions may be rescheduled at the discretion of the investigator when the absence is due to unavoidable circumstances (e.g., acute illness or family emergency), but such rescheduling does not reset the adherence count; (3) Participants show poor compliance, including changes to or receipt of other relevant treatments during the trial; (4) Participants request to withdraw or voluntarily withdraw from the trial during the study period.

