### Data management and quality control

2.10

All clinical data collected by qualified physicians will be entered into a dedicated electronic database, with participant identities replaced by numerical codes. The principal investigator will be responsible for data quality at the study site. Quarterly investigator meetings will address trial-related issues and ensure procedural consistency. Telephone reminders for scheduled visits and assessments will be provided to participants to improve adherence. To monitor adherence to the protocol restriction on unrelated physiotherapy and medications, the following measures will be implemented: (1) participants will be instructed to maintain a daily log recording any additional treatments or medications used during the intervention period; (2) at each study visit (weeks 4, 8, and 12), participants will be systematically asked about their use of other therapies; and (3) weekly telephone calls will be made to reinforce the protocol requirements. Any deviation from the protocol will be recorded in the case report form and reported to the principal investigator. Participants who fail to comply with the protocol will be considered for withdrawal according to the predefined criteria.

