### Statistical analysis

2.12

All statistical analyses will be performed using SPSS version 26.0. Primary analyses will be conducted on an intention-to-treat (ITT) basis, including all randomized participants in their originally assigned groups regardless of protocol adherence or withdrawal. Missing data will be handled via multiple imputation (MI), the gold-standard approach for missing continuous clinical outcome data in randomized controlled trials. Last observation carried forward (LOCF) will not be adopted in the present study, as this single-imputation method is prone to bias and has been widely discouraged in contemporary statistical guidelines. Continuous variables will first be tested for normality using the Shapiro-Wilk test. Normally distributed data will be reported as mean ± standard deviation (SD), whereas non-normally distributed data will be presented as median (first quartile, third quartile) [M (P25, P75)]. For within-group comparisons, paired-sample t-tests will be applied to normally distributed data, and Wilcoxon signed-rank tests to non-normally distributed data. For between-group comparisons at baseline, independent-sample t-tests will be used for normally distributed data, and Mann-Whitney U tests for non-normally distributed data. To compare post-intervention outcomes between the two groups, analysis of covariance (ANCOVA) will be performed, with baseline values as covariates to adjust for potential baseline imbalance. In addition, potential confounding variables—including postpartum duration (months since delivery), age, and baseline outcome values—will be recorded and considered as covariates in the primary analyses where appropriate. Exploratory correlation analyses will employ Pearson or Spearman correlation coefficients, as appropriate, to examine associations among post-intervention pain intensity (NPRS), the Oswestry Disability Index (ODI), the SF-36, core muscle activation (%MVIC), and mean power frequency (MPF). These analyses are hypothesis-generating and will be interpreted with caution; formal corrections for multiple comparisons will not be implemented. All tests will be two-sided, and a *P*-value < 0.05 will indicate statistical significance. Given the exploratory nature of these analyses and the multiple comparisons involved, the results should be interpreted as hypothesis-generating, and any statistically significant findings will require confirmation in future studies.

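### The withdrawal criteria do not separate stopping treatment from leaving follow-up, which works against the promised ITT analysis, and the adherence rule counts 28 Baduanjin sessions where 12 are scheduled

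*Protocol article*

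**What the plan says.** Section 2.4.4 (Withdrawal/dropout criteria) gives four grounds in one list:

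1. "Participants are found not to meet the inclusion criteria after enrollment".
2. "Adherence to the intervention protocol falls below 80" per cent, spelled out as "missing more than 2 of the 12 scheduled manipulation sessions, or more than 5 of the 28 scheduled Baduanjin sessions", and applying only "without a valid reason documented by the investigator".
3. "Participants show poor compliance, including changes to or receipt of other relevant treatments during the trial".
4. The participant's own decision to withdraw.

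Section 2.10 carries the rule into conduct: "Participants who fail to comply with the protocol will be considered for withdrawal according to the predefined criteria". Section 2.12 defines the primary analysis as ITT, "including all randomized participants in their originally assigned groups regardless of protocol adherence or withdrawal", with missing data multiply imputed.

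Two further statements bear on the rule. Inclusion criterion (5) in section 2.4.2 limits other treatment in its own terms: "Participants will not use any unrelated physiotherapy or related medications during the treatment period". The abstract and section 2.7.2 schedule supervised Baduanjin three times a week for 4 weeks, on the same days as manipulation, and section 2.7.2 forbids practice outside those sessions.

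**The concern.** Grounds (1) to (3) can all arise after randomisation, and they stand beside voluntary withdrawal under one heading with no distinction in consequence. Nothing in the article says that a participant removed on these grounds is still assessed at weeks 4, 8 and 12. ITT needs exactly those outcomes. If they are not collected, the participants stay in the analysis set in name, but their values come from the imputation model.

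Low attendance and use of other treatments are plausibly related to pain, which is the primary outcome. Missing values would then arise for outcome-related reasons, and the estimate would drift from the effect of being assigned to the combined programme towards the effect had everyone adhered.

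Separately, an adherence rule whose session count does not match the schedule cannot be applied as written.

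**Working it through.** **1. The rule's own cut-offs.** The limits agree with 80%:
- Manipulation: missing 2 of 12 leaves 10/12 = 83.3%; missing 3 leaves 9/12 = 75%.
- Baduanjin: missing 5 of 28 leaves 23/28 = 82.1%; missing 6 leaves 22/28 = 78.6%.

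**2. The count of 28 against the schedule.** The abstract and section 2.7.2 give 3 × 4 = 12 Baduanjin sessions, and extra practice is forbidden. A participant who attends every session therefore has 12/28 = 42.9% and has missed 28 − 12 = 16, more than 5. Read literally, every experimental participant breaches this limb. Controls have no Baduanjin sessions, so none can.

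**3. When outcomes would be lost.** The first assessment after baseline is week 4 (Table 1), and sEMG is repeated only then. A third missed manipulation session can occur before week 4. A participant removed at that point, and not assessed further, has no post-baseline value at all.

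**4. Possible shift in the estimate (illustration).** The 2-point effect is the planning difference in section 2.11. The other inputs are assumptions: a fraction w of the experimental arm is removed, those removed receive a share f of the added benefit, and imputation returns the adherers' mean. Removals in the control arm are ignored.

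True ITT difference = 2 × (1 − w + w·f). Estimate after imputation ≈ 2. Overstatement = 2 / (ITT difference) − 1.

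| w | f | ITT difference | Overstatement |
|---|---|---|---|
| 0.10 | 0.75 | 2 × 0.975 = 1.95 | 2.6% |
| 0.20 | 0.75 | 2 × 0.950 = 1.90 | 5.3% |
| 0.10 | 0 | 2 × 0.90 = 1.80 | 11.1% |
| 0.20 | 0 | 2 × 0.80 = 1.60 | 25.0% |

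The value f = 0.75 corresponds to benefit in proportion to attendance for someone who came to 9 of 12 sessions, the highest attendance that the manipulation limb still catches. The value f = 0 is the worst case.

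**5. Co-treatment windows.** Section 2.4.2 refers to the treatment period, which is weeks 0–4 in section 2.1. Section 2.4.4 refers to the trial, which is 12 weeks in section 2.1. Section 2.10 has the daily treatment log cover the intervention period but asks about other therapies at weeks 4, 8 and 12. Another treatment first used in week 6 falls outside the first window and inside the second.

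**The case against.** The strongest reply is that the analysis population in section 2.12 is already right, and that no section says assessments stop at withdrawal. Removal is also softened: a documented valid reason exempts a participant, and section 2.10 speaks only of considering withdrawal. The full protocol, which is not shown, may provide for continued follow-up. This stands to the extent that the loss of data is an inference from the heading and the undivided list, not a stated fact. It does not dispose of the point. The article does state a rule that places non-adherence beside voluntary withdrawal, and no later analysis plan can recover outcomes that were never collected. The discretion also lies in a trial where therapists and participants are unblinded (section 2.6).

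On imputation, the model is not given. Some participants below 80% remain because of a valid reason, attendance and co-treatment are recorded and could enter the model, and a participant removed in week 6 may already have a week 4 value. So the shift is a risk whose size depends on the model. It is not a certainty, and a suitable model could reduce it.

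Two stronger readings are tempting and are not supported:

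- **A reader might infer that experimental participants are removed more readily because they can fail two counts and controls only one.** On the stated schedule both components are given at the same visits. Someone who misses whole visits passes the limit of 2 manipulation sessions before reaching a limit of 5 Baduanjin sessions, so the second limb adds nothing. Unequal rates, such as 11.1% against 16.0% at an assumed 10% chance of missing each session, need independent misses over 28 separate Baduanjin sessions, which sections 2.7.2 and 2.11 do not provide for. The asymmetry that the text does contain is the mismatch of 28 with 12.
- **A reader might infer a power gain from about 76% (20 per group) to 85% (25 per group) at SD 2.3.** That comparison keeps a 2-point effect. If retained non-adherers lower the ITT effect to 1.8 or 1.6 points, power with 25 per group is about 77% or 67%. It also blames the whole 20% dropout on this rule, although ground (4) is voluntary.

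The co-treatment wording is a minor inconsistency. Section 2.4.2 is an entry condition and section 2.4.4 a withdrawal ground, and the difference does not by itself show biased missingness.

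**Conclusion.** The point holds as a fault in how withdrawal is fixed. Sections 2.4.4 and 2.10 treat low adherence, co-treatment and later-found ineligibility as dropout without saying that outcome follow-up continues, and on the natural reading this undercuts the ITT analysis in section 2.12. The direction of the likely error is towards the effect under full adherence. Its size cannot be fixed from the article: about 3–5% under proportional benefit and 11–25% under no benefit, both assuming 10–20% of the experimental arm removed and imputation that reproduces adherers.

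The mismatch of 28 counted with 12 scheduled Baduanjin sessions needs no assumption. It is a contradiction within the article and makes that limb of the rule unusable as written. The case for change rests on the validity of the ITT estimate, not on power or on a general imbalance between arms.

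**What to change.** - State in sections 2.4.4 and 2.10 that meeting grounds (1) to (3) does not end outcome follow-up. Keep the already scheduled NPRS, ODI and SF-36 at weeks 4, 8 and 12 and sEMG at week 4, unless consent is withdrawn or contact is lost, and analyse each participant in the randomised arm. Whether study treatment stops remains a separate decision for the investigator.
- Use the adherence and co-treatment criteria only to define a supportive per-protocol set.
- Reconcile the 28-session count in section 2.4.4 with the 12-session schedule in the abstract and section 2.7.2.
- Reconcile the co-treatment window across sections 2.4.2, 2.4.4 and 2.10.

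The cost is a change of wording and a few more participants kept in visits that are already planned. The ITT estimate may come out smaller, but it will be the one that section 2.12 promises.
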